# Oral health care during pregnancy to prevent preterm birth and low birth weight: study protocol for a randomized controlled trial

**DOI:** 10.1186/s13063-025-09355-y

**Published:** 2025-12-10

**Keywords:** Preterm birth, Low birth weight, Oral health, Periodontal treatment, Chlorhexidine gluconate mouthwash, Randomized controlled trial, Bangladesh

## Abstract

**Background:**

Periodontal disease during pregnancy has been associated with an increased risk of preterm birth (PTB) and low birth weight (LBW). However, most previous interventional studies have reported that scaling and root planing (SRP), a form of basic periodontal treatment, is insufficient to effectively prevent PTB and LBW. Recent systematic reviews and meta-analyses suggest that combining SRP with routine use of chlorhexidine gluconate (CHG) mouthwash may reduce the risk of these adverse birth outcomes by approximately half. This study will be among the first randomized controlled trials (RCTs) to evaluate the potential synergistic effects of this combined approach on improving birth outcomes.

**Methods:**

This multi-center, three-arm RCT will be conducted at two hospitals in Dhaka and Bogura, Bangladesh, between April 2025 and September 2026. A total of 480 pregnant women less than 20 weeks’ gestation attending antenatal checkups will be recruited. Participants diagnosed with periodontal disease will be randomly assigned to either an intervention group or a positive control group. Participants without periodontal disease will be assigned to a negative control group. The intervention consists of SRP combined with continued use of CHG mouthwash throughout pregnancy. The primary outcome will be the rate of PTB. Secondary outcomes include the birth weight of the newborn baby, maternal periodontal status, and oral health-related quality of life (OHRQoL). Effectiveness will be assessed by comparing outcomes across the study groups.

**Discussion:**

The oral health intervention is expected to improve both birth outcomes and maternal oral health. Demonstrating its effectiveness in a real-world setting may support the integration of oral health care into broader maternal, neonatal, and child health strategies, particularly in resource-limited settings.

**Trial registration:**

UMIN Clinical Trials Registry. UMIN000057519. Registered on April 4, 2025. https://center6.umin.ac.jp/cgi-open-bin/ctr/ctr_view.cgi?recptno=R000065719.

**Supplementary Information:**

The online version contains supplementary material available at 10.1186/s13063-025-09355-y.

## Background

More than 60 countries are currently off track to meet the Sustainable Development Goal target of reducing the neonatal mortality rate to 12 or fewer per 1000 live births by 2030 [1, 2]. Among the major contributors to neonatal and infant mortality are preterm birth (PTB), defined as birth before 37 weeks of gestation, and low birth weight (LBW), defined as a birth weight of less than 2500 g [1]. PTB alone accounts for approximately 40% of neonatal deaths [2, 3], while LBW and prematurity together contribute to an estimated 60–80% of global neonatal mortality [4, 5]. Moreover, both PTB and LBW are associated with long-term adverse health outcomes. Infants born preterm are at increased risk of cerebral palsy, cognitive impairment, and developmental abnormalities [6, 7]. Babies born with LBW face higher risks of chronic noncommunicable diseases in adulthood, including cardiovascular diseases, type 2 diabetes, and hypertension [8, 9].

To address these issues, strengthening the continuum of care (CoC) in MNCH services is strongly recommended [10]. The MNCH CoC framework aims to ensure access to essential health services throughout the life course by providing all women with access to reproductive health care before and during pregnancy and childbirth, and by ensuring that newborns receive the care necessary for healthy growth [11]. Systematic reviews and meta-analyses have consistently shown that ensuring CoC is critical for enhancing MNCH outcomes, especially in low- and middle-income countries [12, 13]. Furthermore, recent research has advocated for integrating additional health programs, such as noncommunicable disease prevention and treatment, into the MNCH CoC to strengthen its impact [14].

Emerging evidence suggests that poor oral health, particularly periodontal disease, may adversely affect overall health, including MNCH outcomes such as PTB and LBW [15, 16]. Pregnancy often exacerbates oral health problems due to hormonal changes, especially elevated estrogen and progesterone levels, which impair immune responses and lead to increased vascular permeability and gingival inflammation [17]. A systematic review and meta-analysis of 20 studies found that the global prevalence of periodontal disease among pregnant women is approximately 40% [18].

Epidemiological studies have proposed both direct and indirect pathways through which periodontal disease may contribute to adverse birth outcomes [19–21]. In the direct pathway, periodontal pathogens can reach fetal-placental tissues via hematogenous dissemination, triggering local inflammation and tissue damage that lead to pregnancy complications. In the indirect pathway, inflammatory cytokines and mediators from the gingiva and/or acute-phase reactants from the liver accumulate in the intrauterine compartment, exacerbating inflammation and contributing to pregnancy complications [20, 22]. The adverse impact of periodontal disease on pregnancy outcomes tends to worsen as the severity of maternal periodontal inflammation increases [23, 24].

Both MNCH and oral health require urgent public health attention in Bangladesh. In 2020, Bangladesh had the highest rate of PTB in South Asia at 16.2% [25]. The prevalence of LBW has remained persistently high at 25.7% in 2000, 24.5% in 2010, and 23.0% in 2020 [26]. The most recent figure exceeds that of many other developing countries [1]. The country’s neonatal mortality rate was reported at 20 deaths per 1000 live births in 2022 [27], which is significantly higher than the SDG target. Data on oral health are scarce, particularly in pregnant women, who are at high risk of developing periodontal diseases. A recent cross-sectional study in Dhaka reported that 95.3% of pregnant women had periodontal disease, with 52.4% diagnosed with gingivitis and 43% with periodontitis [28].

Although the relationship between oral health during pregnancy and birth outcomes has garnered increasing attention, effective oral care strategies for the prevention of PTB and LBW remain underexplored. Most interventional studies have found that basic periodontal treatment, which consists of scaling to remove plaque and calculus above the gingival margin and root planing to remove calculus below the gingival margin, is insufficient to prevent PTB and LBW [29, 30]. However, recent systematic reviews and meta-analyses suggest that combining scaling and root planing (SRP) with routine oral care using mouthwash containing chlorhexidine gluconate (CHG) may reduce the risk of PTB and LBW by approximately half (PTB: RR = 0.56; LBW: RR = 0.47) [31]. Another review found that the same combination significantly reduced the risk of PTB (OR = 0.29) and the composite outcome of PTB and/or LBW (OR = 0.18) [32]. The most recent meta-analysis further supported the effectiveness of combining SRP with any mouthwash, reporting a pooled RR of 0.44 for PTB and 0.33 for LBW [33]. Despite these promising results, there remains a lack of well-designed randomized controlled trials (RCTs) to confirm the effectiveness of this combined approach [31–33].

Given the urgent need to establish effective oral health management strategies for pregnant women, integrating oral health care into the MNCH CoC represents a promising and potentially scalable approach. This study therefore aims to (1) assess whether the association between periodontal disease and adverse birth outcomes observed in previous research is also evident in our study population, and (2) evaluate the effectiveness of an integrated intervention, combining SRP and CHG mouthwash use, delivered through MNCH CoC, in preventing PTB and LBW. This RCT will also examine the intervention’s impact on maternal periodontal status and oral health-related quality of life (OHRQoL). Demonstrating the effectiveness of this intervention could provide critical evidence for incorporating oral health into broader MNCH strategies. We believe this study offers a unique and timely contribution to improving MNCH outcomes through an oral health approach.

## Methods

### Study design

This study is a multi-center, three-arm RCT, consisting of one intervention group (group A) and two control groups (group B and C). The trial is designed in accordance with the Standard Protocol Items: Recommendations for Intervention Trials (SPIRIT) statement. Figure 1 shows a flow chart of the study design, including baseline and endline surveys, dental checkups, and intervention. Figure 2 summarizes the timeline of enrolment, interventions, and assessments, as per the SPIRIT flow diagram.

**Fig. 1 Fig1:**
[figure not shown]
Flow chart of the study

**Fig. 2 Fig2:**
[figure not shown]
Schedule of enrolment, interventions, and assessments (SPIRIT flow diagram)

### Study sites

This trial will be conducted from April 2025 to September 2026 at two hospitals in Bangladesh: Holy Family Red Crescent Medical College Hospital (HFRC) in Dhaka and TMSS Medical College & Rafatullah Community Hospital (TMSS) in Bogura. Both the obstetrics and gynecology, and dental departments of each hospital will implement the interventions. Research coordinators from Grameen Communications will oversee overall coordination.

### Study population

Pregnant women attending antenatal checkups will be recruited from the obstetrics and gynecology departments at both hospitals, targeting approximately 225 participants per site. Enrollment will continue until 160 participants are allocated to each study group. Trained healthcare professionals, such as doctors, dentists, nurses, midwives, and dental assistants, who have completed a training program led by the research team, will assess eligibility, explain the study procedures, obtain informed consent, and conduct the intervention.

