### Sample size calculation

Assuming a baseline PTB rate of 16.2% [25], and expecting the intervention to reduce this to 4.7% [32], a sample size of 128 per group is required to detect this difference with 80% power at a 5% significance level. Accounting for a 20% attrition rate, the total sample size is set at 480 (160 per group).

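### Enrolment runs until all three groups hold 160, but disease prevalence sets the size of group C, and neither prevalence the protocol cites yields 160 per group from the stated 480 women

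*Protocol article*

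**What the plan says.** The Study population section sets a site target, "targeting approximately 225 participants per site", and then the rule that ends recruitment: "Enrollment will continue until 160 participants are allocated to each study group". Study sites places the trial "at two hospitals in Bangladesh", in Dhaka and Bogura. Sample size calculation reads "Accounting for a 20% attrition rate, the total sample size is set at 480 (160 per group"), and the Abstract (Methods) says "A total of 480 pregnant women less than 20 weeks’ gestation attending antenatal checkups will be recruited".

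Under Randomization and blinding, and again under Diagnosis of periodontal disease, women with periodontal disease are randomised to A or B and women without it go to C. The case definition covers gingivitis as well as periodontitis.

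The Background gives two prevalences. A Dhaka study found that "95.3% of pregnant women had periodontal disease" (52.4% gingivitis, 43% periodontitis), and a review of 20 studies put the "global prevalence of periodontal disease among pregnant women is approximately 40" percent. Trial status gives a recruitment window from 27 April 2025 to December 2025, about eight months.

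Aim 1, the association between periodontal disease and adverse birth outcomes, is assessed by comparing B with C (Background and Statistical analyses).

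**The concern.** An investigator can fix the ratio of A to B, because it is randomised. The ratio of C to A plus B cannot be fixed in the same way, because it follows from how many of the women examined have disease. A rule that waits for 160 in every group therefore commits the trial to examining however many women the slowest group requires. The article states 480 as though that were both the number recruited and the number allocated.

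At stake is mainly aim 1. If enrolment stops near the planned total and prevalence is as high as the Dhaka figure, C is too small to say much about B versus C. If enrolment runs on until C fills, with A and B closed at 160, most of C is recruited after B has closed, and disease status is confounded with calendar time. If A and B stay open, they grow far beyond 160. At low prevalence the shortfall moves to A and B, which carry the primary comparison.

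**Working it through.** **Inputs.** Sites: 2. Target per site: about 225. Group size: 160. Preterm birth: 16.2% versus 4.7%. Power 80%, significance level 5% (taken as two-sided), attrition 20%. Prevalence of disease: 95.3% and about 40%, both cited. My assumptions: a prevalence of 80% as a middle value, and a preterm birth rate of 8.1% in C (half of 16.2%), since the protocol gives none.

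**1. The plan's own figure.** The two-proportion formula with pooled variance gives 110 per group. With continuity correction, n' = (n/4) × [1 + √(1 + 4/(n × d))]², where d = 0.162 − 0.047 = 0.115. So (110/4) × [1 + √(1 + 4/12.65)]² = 27.5 × 4.61 ≈ 127, against the stated 128. Then 128/0.8 = 160, and 3 × 160 = 480. The sample size reproduces.

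**2. Site target.** 2 × 225 = 450, which is 30 short of 480 (6.25%).

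**3. Prevalence that yields equal groups.** A and B together need 320 of 480: 320/480 = 66.7%.

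**4. Group sizes at other prevalences.** With prevalence π:
- women examined when A and B are full = 320/π
- C at that point = 320 × (1 − π)/π
- C among 480 = 480 × (1 − π)
- women examined for 160 in C = 160/(1 − π)

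| π | Examined to fill A and B | C at that point | C among 480 | Examined to fill C |
|---|---|---|---|---|
| 95.3% (cited, Dhaka) | 336 | 16 | 23 | 3,404 |
| 80% (assumed) | 400 | 80 | 96 | 800 |
| 66.7% (break-even) | 480 | 160 | 160 | 480 |
| 40% (cited, global) | 800 | 480 if uncapped | 288 | 267 |

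At 95.3% the 95% binomial range for C among 480 is 14 to 32. Filling C takes 3,404/480 ≈ 7 times the planned number, in about eight months. Of those women, 3,404 − 160 = 3,244 have disease. If A and B close at 160 each, 3,244 − 320 = 2,924 have no group to enter. If they do not close, each reaches about 1,622.

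At 40%, 480 women leave 480 × 0.40/2 = 96 in each of A and B.

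**5. Precision of B versus C at 95.3%.** After 20% attrition, 16 to 23 in C become about 13 to 18, against 128 in B. The 95% half-width is 1.96 × √[0.162 × 0.838/128 + 0.081 × 0.919/n_C]:
- n_C = 13: 1.96 × √(0.00106 + 0.00573) = 16 points
- n_C = 18: 1.96 × √(0.00106 + 0.00414) = 14 points
- n_C = 128: 1.96 × √(0.00106 + 0.00058) = 8 points

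The normal approximation is rough at 13 to 18 women, but the loss of precision is plain.

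**6. A versus B at 95.3%.** A and B fill after about 336 women, well inside 480, so the primary comparison keeps its planned size.

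**The case against.** The rule is an open quota. At any prevalence strictly between 0 and 100% it reaches 160 in each group if enough women are examined, and 480 can be read as the number allocated. A reader might infer that the rule cannot deliver the groups at all; the documents do not support that. The question is feasibility within the stated total and window. Still, the Abstract says that 480 women will be recruited, and consent precedes the dental checkup, so the article does not separate women examined from women allocated.

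The site target is worded as approximate, and the Abstract, Study population and Sample size calculation agree on 480 or 160 per group. The gap of 30 is therefore minor. A reader might go further and infer that the primary analysis is underpowered, because 450/3 = 150 per group leaves 120 after attrition, below 128. That needs exactly equal groups and recruitment that stops on the site targets, which the quota sentence rules out. At 95.3%, even 450 women give about 429 with disease, or 214 per arm if uncapped and about 171 after attrition.

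The 95.3% is a background citation from one city, not a design assumption. Its case definition is not visible, Bogura may differ, and the trial excludes high-risk pregnancies. This is fair, and the middle row of the table shows a milder result. But the Dhaka figure is the only local one cited and, like the trial's definition, includes gingivitis. A low Bogura prevalence would not help much: with 240 women per site, Dhaka supplies 240 × 0.047 ≈ 11 to C, so Bogura must supply about 149, which requires a prevalence of about 38% there. Group C would then be about 93% Bogura women, confounding disease status with site.

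Caps and screening numbers are often left to the full protocol, and the flow chart is not shown. Their absence is not counted as an error here. The point rests on the stopping rule, total and prevalences that the article itself states.

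Finally, a reader might want a power figure for B versus C. Power is low on every basis tried, but its value depends on the variance formula and on an assumed rate in C, so interval width is the safer measure.

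**Conclusion.** The point holds as a question of feasibility and internal consistency. Equal groups of 160 from 480 women require a prevalence of about 67%, and both cited prevalences miss it, in opposite directions. At 95.3% the harm falls on aim 1, the non-randomised comparison: about 16 to 23 women in C, and a half-width of about 14 to 16 points instead of about 8, given the assumed 16.2% versus 8.1%. The randomised comparison of A with B is unharmed at that prevalence. At 40% it would be the one left short, at 96 per arm, if enrolment ended at 480. At an assumed 80%, C holds about 80 when A and B fill. The 450 against 480 is a small inconsistency that needs only correcting. The change is worth making, because following the rule as written would either overrun the planned total or, if recruitment stops at 480, leave one of the comparisons well below its planned size.

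**What to change.** 1. Tie the end of enrolment to 160 women in each of A and B.
2. Enrol C concurrently, up to 160, and close it when A and B are full.
3. Make the per-site target and the total agree with this rule, and state the expected number examined over a range of prevalences, for example 40% to 95.3%.
4. Restate aim 1 as estimation, with a confidence interval at whatever size C reaches.
5. Optionally, add a supportive analysis of preterm birth by baseline periodontal severity within B. It estimates a gradient among women with disease and does not replace B versus C.

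The cost is protocol wording, possibly one extra analysis, and a less favourable stated size for C. At high prevalence the change does not enlarge C; it makes the limited information on aim 1 explicit and keeps B and C recruited over the same period. It adds no women to the planned allocation. The number to be examined still depends on prevalence, and at 40% it would be about 800.

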### Inclusion and exclusion criteria

Eligible participants will include pregnant women aged 18 years or older, with a gestational age of less than 20 weeks at recruitment. Women with multiple or high-risk pregnancies, as confirmed by attending healthcare professionals, will be excluded. High-risk conditions include diabetes, epilepsy, seizure disorders, and hypertension.

#### Hypothesis

We hypothesize that integrating an intervention targeting periodontal disease—comprising SRP and CHG mouthwash use—into the MNCH CoC will reduce PTB and LBW, decrease the prevalence of periodontal disease, and improve OHRQoL.

### Randomization and blinding

The trial includes three groups: group A (intervention) and groups B and C (control). All participants will first complete a face-to-face interview at the obstetrics and gynecology department following consent. They will then undergo a baseline dental checkup. Participants diagnosed with periodontal disease will be randomized to group A or B using blocked randomization via computer-generated sequence at each site. Those without periodontal disease will be assigned to group C.

Blinding will be maintained for the interviewers and data recorders, who will not be informed of group allocation. However, blinding will not be feasible for the dentists conducting dental checkups or for participants due to the nature of the intervention.

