#### Basic periodontal treatment and mouthwash use

Participants in group A will receive SRP and CHG mouthwash immediately after baseline dental checkups. Group B will receive the same intervention after the endline checkup. SRP procedures will take 10 to 15 min per patient. CHG use involves rinsing after morning and evening toothbrushing. Participants will log their daily hygiene practices in the provided handbook. Group A will receive follow-up dental cleaning using a toothbrush during subsequent antenatal visits.

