### Data collection and study outcomes

The primary outcome is PTB (< 37 weeks gestation). Secondary outcomes include LBW (< 2500 g), periodontal disease, and OHRQoL.

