#### Dental checkups

Dental checkups (approximately 10 min per participant) will be conducted at both baseline and endline to collect dental data and diagnose periodontal disease [43]. A full-mouth examination will be performed to assess overall oral hygiene status, evaluating the condition of the teeth (sound, carious, treated, or missing), bleeding on probing (BOP), probing pocket depth (PPD), clinical attachment loss (CAL), plaque, calculus, tooth mobility, and oral dryness. BOP is defined as the presence or absence of bleeding during examination of the periodontal pocket. PPD refers to the distance from the gingival margin to the bottom of the pocket, while CAL is the distance from the cemento-enamel junction to the bottom of the pocket [44–46]. Oral dryness will be assessed using a classification scale based on the condition of the tongue mucosa, with higher grades indicating more severe dryness [47].

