##### Diagnosis of periodontal disease

BOP, PPD, and CAL will be measured at six points on each tooth and used to diagnose periodontal diseases, including gingivitis and periodontitis. Gingivitis is diagnosed when BOP is present at 10% or more of the total number of periodontal sites examined. Periodontitis will be diagnosed if either of the following criteria is met: (1) interdental CAL is observed at ≥ 2 non-adjacent teeth, or (2) a buccal or palatal/lingual site exhibits a CAL of ≥ 3 mm and PPD of ≥ 4 mm at ≥ 2 teeth [45, 46].

Participants diagnosed with periodontal disease will be randomized into either the intervention group A or control group B. Participants without periodontal disease will be allocated to control group C.

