## Discussion

This protocol describes a RCT to be conducted at two hospitals in Bangladesh, aiming to evaluate the effectiveness of integrating an oral health intervention into the MNCH CoC for the prevention of adverse birth outcomes. Specifically, this study investigates whether a combination of basic periodontal treatment (SRP) and the continued use of CHG mouthwash during pregnancy can prevent PTB and LBW. Although the association between oral hygiene and various systemic conditions has garnered increasing attention, the effective oral care methods for preventing adverse birth outcomes remain unclear. Most previous interventional studies have demonstrated that SRP alone is insufficient to significantly reduce the risk of PTB and LBW [29, 30].

At present, strategies to manage periodontal disease during pregnancy and promote oral health care for mothers and children have not been incorporated into the MNCH CoC framework or the World Health Organization’s guidelines for antenatal and postnatal care. In light of the increasing recognition of the importance of maternal oral hygiene, there is a need for a more proactive and sustained approach to oral health. The effectiveness of such an approach may be particularly evident in resource-limited settings, where MNCH indicators remain suboptimal.

This study has some limitations. First, the sample will consist solely of pregnant women in Bangladesh, recruited from two regions (Dhaka and Bogura), which may limit the generalizability of the findings due to potential sampling bias. Second, because of the nature of the intervention, blinding of the dentists performing the baseline dental assessments and the participants will not be feasible. To minimize the risk of assessment bias, endline dental checkups will be performed by independent dentists who were not involved in the baseline dental checkups.

Despite these limitations, demonstrating the effectiveness of this oral health intervention in a real-world setting could provide valuable insights into the potential contribution of oral care to improving MNCH outcomes, particularly in low-resource environments.

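### The article disagrees with itself on whether endline dental examiners can be blinded and never says they are masked, leaving the secondary periodontal outcome open to avoidable detection bias

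*Protocol article*

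**What the plan says.** The section Randomization and blinding divides people into two classes. On one side: "Blinding will be maintained for the interviewers and data recorders, who will not be informed of group allocation". On the other: "blinding will not be feasible for the dentists conducting dental checkups or for participants due to the nature of the intervention". That second statement is not restricted to either time point, and the Dental checkups section says that the checkups "will be conducted at both baseline and endline to collect dental data and diagnose periodontal disease".

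The Discussion, listing limitations, words the matter differently: "blinding of the dentists performing the baseline dental assessments and the participants will not be feasible". It then offers a safeguard against assessment bias: "endline dental checkups will be performed by independent dentists who were not involved in the baseline dental checkups".

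The section on how the diagnosis is made describes the measurements at issue: "BOP, PPD, and CAL will be measured at six points on each tooth and used to diagnose periodontal diseases, including gingivitis and periodontitis". The outcome's rank is given under Data collection and study outcomes: "Secondary outcomes include LBW (< 2500 g), periodontal disease, and OHRQoL". On the timing of the control group's treatment, the section Basic periodontal treatment and mouthwash use says: "Group B will receive the same intervention after the endline checkup".

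**The concern.** A site following the blinding section would treat the endline dentists as people who cannot be blinded and would take no steps to keep the arm from them. A site following the Discussion would use different dentists at endline but would still have no instruction to mask them. Under either text, an endline examiner may know the arm while probing.

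That matters because the diagnosis is made by hand against cut-offs: bleeding at 10% or more of sites for gingivitis, and attachment loss (with a 3 mm limit at buccal or lingual sites) combined with a 4 mm pocket depth for one of the two routes to periodontitis. A small shift in probing or reading near a cut-off changes a woman's classification. Reduced periodontal disease is part of the trial's stated hypothesis, and endline status enters the mixed-effects comparison of groups A and B. Blinding the data recorder does not help, since the recorder writes down what the dentist has already judged.

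**Working it through.** The point rests on no figure in the article, so the check is mainly a comparison of sections.

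**1. Who is covered by the infeasibility statement?**
- Randomization and blinding: all dentists who conduct checkups.
- Dental checkups: checkups take place at baseline and at endline. Taken together, these two sections include the endline dentists.
- Discussion: only the dentists at the baseline assessment, with the participants.

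The first two sections and the third cannot both be the intended rule.

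**2. Is masking of the endline dentists stated anywhere?** No. The only people listed as blinded are interviewers and data recorders. The Discussion calls the endline dentists independent, and it defines this as not having taken part at baseline. An examiner can be new to the participant and still know her group.

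**3. At which checkup can knowledge of the arm matter for A versus B?** The order is consent, interview, baseline checkup, then randomisation of women with periodontal disease. At baseline no A or B allocation exists yet. At endline it does.

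In symbols, let p be the true endline proportion with disease, the same in both arms, and let Se and Sp be the examiner's sensitivity and specificity in each arm. The observed proportion in an arm is

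Se × p + (1 − Sp) × (1 − p),

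so with no true effect the observed difference A − B is

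(Se_A − Se_B) × p − (Sp_A − Sp_B) × (1 − p).

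If a masked examiner reads both arms alike, Se_A = Se_B and Sp_A = Sp_B, and the expression is zero. If knowledge of the arm shifts either one, it is generally not zero. Its sign depends on which way the examiner leans. The article gives no value for endline p, Se or Sp in either arm, so neither size nor direction can be calculated.

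**4. Does the endline examiner need to know the arm?** Nothing described requires it. Group B's treatment follows the endline checkup, so the findings can be recorded before the group is opened. The stated reason, the nature of the intervention, explains why participants and anyone giving the treatment know the arm. It does not by itself explain why a separate dentist who only measures must know it.

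**5. Which outcomes are reached?** Periodontal disease is. Gestational age at delivery and birth weight are taken from antenatal records, so the primary outcome and low birth weight are not directly touched. The sample size (128 per group, 160 after attrition) is set on preterm birth and would not change.

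**The case against.** The strongest reply is that the authors saw the risk and placed a safeguard where it counts. Group A is treated straight after the baseline checkup, so dentists present then may treat participants or learn their arm, and the Discussion keeps those dentists away from the endline examination. This stands. A reader might infer that the plan protects the wrong examination altogether, but the text shows an incomplete safeguard at the right one.

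Second, the Discussion is the more specific passage and can be read as leaving the endline dentists outside the group that cannot be blinded. A reader might therefore infer too much in taking it as settled that they will be unmasked. What the article supports is that its sections differ and that masking is not stated.

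Third, a reader might infer that masking is withheld without any reason. The article does give one, although it fits a separate endline examiner poorly. Full masking may also be out of reach: participants know their arm, and the checkup records plaque and calculus, so the mouth itself may suggest treatment. This limits how well masking can work but is no ground for not attempting it.

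Fourth, it is tempting to name the routes by which the arm would leak, such as the treatment chart or the handbook. Groups do receive different handbooks, but nothing says that endline dentists see them or the chart.

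Fifth, the statement about baseline holds only for A versus B. Group C is formed from the baseline findings, so the baseline dentist's judgement does matter for the comparison of B with C.

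Finally, a condensed article may leave masking procedures to the full protocol. That excuses missing operational detail. It does not excuse two published sections that give different rules.

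**Conclusion.** The point holds in a limited form. The blinding section, read with the description of the checkups, covers endline dentists, whereas the Discussion restricts the problem to baseline dentists and relies on independence without masking. For A versus B, the endline examination is where knowledge of allocation can matter, and independence from the baseline checkup protects only in part. The secondary periodontal outcome is therefore exposed to avoidable detection bias. A reader might infer that the result will be biased, and in favour of treatment. The article supports exposure only, since it contains no data on examiner error or endline prevalence and any figure would rest on invented inputs. Preterm birth and birth weight are not directly affected. The conclusion assumes that the full protocol contains no masking instruction at odds with the published text. If it does contain one, the article needs only to be brought into line with it.

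**What to change.** Reconcile Randomization and blinding with the Discussion. State in the former that the independent endline dentists are masked to allocation, and that group and treatment records are withheld from them until the endline form is complete and before any deferred treatment of group B. Confine the infeasibility statement to the people it actually fits. Add to the limitations that masking may be imperfect because participants know their arm and signs of treatment may be visible.

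The cost is small: separate endline dentists are already planned, the existing order of checkup and group B treatment allows it, and the sample size is unchanged. Recruitment began in April 2025 and data collection is expected to run to September 2026, so some endline checkups may already have been done. If those were not masked, the report should say from what date masking applied.
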